**Methods:**

Following an initial 2 years of SEI, patients are randomized to receive either 3-years of continued SEI or regular care. SEI provided at three sites within the McGill network of SEI services, using a model of treatment comprised of: modified assertive case management; psycho education for families; multiple family intervention; cognitive behavioural therapy; and substance abuse treatment and monitoring. Blinded research assistants conduct ongoing evaluation of the outcome variables every three months. The primary outcome measure is remission status measured both as the proportion of patients in complete remission and the mean length of remission achieved following randomization during the additional three years of follow up. Based on preliminary data, it is determined that a total of 212 patients are needed to achieve adequate statistical power. Intent to treat with the last observation carried forward will be the primary method of statistical analysis.

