### Assessments

Evaluations and assessments are carried out at entry and every three months thereafter for the entire follow up period, or until withdrawal from the study, for both treatment conditions (details of assessments are provided in Table 1). If a patient withdraws, they are asked to provide one last assessment. When no contact has been made for 3 consecutive assessment periods (for a total of 9 months) and attempts made for contact through phone calls, emails, and contact with care providers including family members, are not successful, the patient is considered to be withdrawn. Trained evaluators will conduct assessments largely through a semi structured interview format.

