**Table 1 Tab1:** **Assessment instruments**

**Assessment**	**Instrument**
Psychopathology	Scale for the Assessment of Positive Symptoms (SAPS) [41]*
	Scale for the Assessment Negative Symptoms (SANS) [42]*
	Positive and Negative Syndrome Scale (PANSS) [43]*
	Brief Psychiatric Rating Scale (BPRS) [44]*
Functioning	Global Assessment of Functioning Scale (GAF) [45]*
	Social and Occupational Functioning Scale (SOFAS) [46]**
	Productivity Interview Questionnaire (adapted from the Client Socio-Demographic and Service Receipt Inventory) [47]*
	Life Skills Profile [48]**
Medication and side effects	Patient Compliance Interview [49]*
	Medication Compliance: Pill Count Form [49,50]*
Substance use	Chemical Use/Abuse/Dependence-Scale (CUAD) [51]*
	Time Line Follow Back [40]*
Working alliance	Working Alliance Inventory (WAI) [52]**
Randomization preference	Self administered questionnaire***
Quality of life	Life Satisfaction and Psychological Well-being domains of the Wisconsin Quality of Life-Client version [53]**
Duration of untreated psychosis	Circumstances of Onset and Relapse Schedule (CORS) [11]***
Promorbid adjustment	Premorbid Adjustment Scale (PAS) [52]***
Service use including hospital admittance and total bed days	Self administered questionnaire with list of services received
	Regie de l’Assurance-maladie du Quebec (Quebec medical insurance; RAMQ)****
	Med-Echo (for hospitalizations)****

*Assessed at each evaluation (every 3 months).

**Assessed at every second evaluation (every 6 months).

***Assessed once at baseline.

****Assessed post study completion.

Data on the Duration of Untreated Psychosis (DUP) are available for all PEPP patients and is derived using the Circumstances of Onset and Relapse Schedule (CORS) [11], a structured interview instrument for use with patients and families that includes some sections from the Interview for the Retrospective Assessment of Onset of Schizophrenia (IRAOS) [54]. DUP data for all other patients is available through chart verification.

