### Primary outcome

The primary outcome is complete remission measured as both the proportion of patients in remission, as well as the mean length of remission achieved following randomization during the additional three years of follow up. Complete remission is defined according to consensus criteria as a rating of mild or less on the following positive and negative symptom scale items (Positive domain: hallucinations, delusions, bizarre behaviour, positive formal thought disorder; Negative domain: affective flattening or blunting; alogia; avolition-apathy; anhedonia-asociality) for a period of six months [55]. Complete remission is chosen as the primary outcome measure as per findings that remission across both symptom domains is a better predictor of functional outcome than remission of positive symptoms alone [56,57]. Remission is measured at each assessment covering the three months prior using the Scale for Assessment of Positive Symptoms [41] and the Scale for the Assessment of Negative Symptoms [42]. The SANS domain of Attention is not included in SANS ratings as these items have not been shown to correlate to the domain of negative symptoms [58].

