### Statistical analyses

Data analysis is based on the intent to treat principle. All patient evaluations will be included in the analysis. To assess homogeneity at baseline, relevant demographic data will be presented.

For the primary outcome measures, the proportion of patients in remission in the experimental and control groups will be compared using a Pearson chi-square statistic and the mean length of remission with a t-test or Wilcoxon test for independent samples, based on the distribution of the independent variable. Logistic regression analyses and multiple regression analyses will also be performed with all covariates and mediators.

For the secondary outcome measures including relapse (relapse vs. no relapse), dichotomous outcomes will be analyzed using logistic regression with covariates. Time to Event (relapse) will be measured using a Kaplan-Meier methods and Cox regression to analyze intervals of time from randomization to relapse. Continuous outcomes that include clinical outcomes will be assessed using regression models with covariates and finally longitudinal data with repeated measurements will be analyzed using repeated measures of analysis of variance.

Missing data will be assessed to determine if they are random or informative. Should missing data be non ignorable, then selection models and pattern-mixture models will be used to evaluate the robustness of the primary analyses.

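### Repeated-measures ANOVA for the longitudinal secondary outcomes either drops about a fifth of patients, unequally by arm, or leans on last observation carried forward, which the analysis section does not mention

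*Protocol article*

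**What the plan says.** All of the following is in the protocol article.

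- **Method.** Statistical analyses: "longitudinal data with repeated measurements will be analyzed using repeated measures of analysis of variance".
- **Principle, same section.** "Data analysis is based on the intent to treat principle", and "All patient evaluations will be included in the analysis".
- **Missing-data rule.** The Methods paragraph of the abstract says: "Intent to treat with the last observation carried forward will be the primary method of statistical analysis". The Statistical analyses section does not mention LOCF.
- **Sensitivity analysis.** If missingness proves non-ignorable, "selection models and pattern-mixture models will be used to evaluate the robustness of the primary analyses". The secondary outcomes are not named.
- **Schedule.** Assessments: "Evaluations and assessments are carried out at entry and every three months thereafter for the entire follow up period". Follow-up covers three years after randomization. Table 1 puts SAPS, SANS and GAF on the quarterly schedule. SOFAS, the Life Skills Profile and quality of life carry the footnote "Assessed at every second evaluation (every 6 months".
- **Attrition.** Power and sample size expects 25% in the control arm and below 20% in the experimental arm.
- **Dropout.** Participant withdrawal counts a patient as a dropout only after three consecutive missed assessments.

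**The concern.** Classical repeated-measures ANOVA needs a value at every occasion from every patient it analyses. A patient who leaves in the third year loses all earlier visits from the analysis as well, and one missed visit has the same effect. The dropout definition allows a retained patient to miss one or two visits in a row, so the plan itself foresees gaps beyond dropout.

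The method therefore sits badly beside the promise to use all evaluations. The outcomes at stake are symptom levels, functioning and quality of life, which carry secondary hypothesis (c) in the Background. A completer set that is selected differently in the two arms no longer has the protection of randomization, and the discarded visits cost precision.

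Filling the gaps by LOCF removes the exclusion but brings a different problem. The trial's premise is that gains fade after transfer to regular care. Holding a control patient's last value constant assumes no such change after that patient leaves.

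**Working it through.** **Occasions.** Quarterly scales: 1 + 36/3 = 13. Six-monthly scales: 1 + 36/6 = 7. Post-entry visits are 12 and 6.

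**The plan's attrition allowance.** The mean of 25% and 20% is 22.5%. Inflating 164 gives 164/(1 − 0.225) = 211.6, so 212, as stated. The implied loss is 1 − 164/212 = 22.6%. The attrition figure is thus the one the plan itself uses.

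**Loss from dropout alone, no imputation.** Trial status gives 109 experimental and 111 control patients.

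- Experimental attrition at its ceiling of 20%: 109 × 0.20 + 111 × 0.25 = 21.8 + 27.75 = 49.6 patients, or 22.5% of 220.
- Experimental attrition of 15% (assumed, since the text says only below 20%): 16.35 + 27.75 = 44.1 patients, or 20.0%.

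In both cases the control arm loses the larger share.

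**Adding isolated missed visits.** The protocol gives no rate. Assume a probability m of missing any one post-entry visit among retained patients, independent across visits, with overall dropout of 22.5%. The complete share is 0.775 × (1 − m)^k, with k = 12 or 6.

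| m (assumed) | Quarterly, k = 12 | Six-monthly, k = 6 |
|---|---|---|
| 0% | 77.5% | 77.5% |
| 2% | 61% | 69% |
| 3% | 54% | 65% |
| 5% | 42% | 57% |

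The rate at which half the patients are lost solves 0.775 × (1 − m)^k = 0.5:

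- k = 12: m = 1 − (0.5/0.775)^(1/12) = 3.6%
- k = 6: m = 1 − (0.5/0.775)^(1/6) = 7.0%

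If misses cluster in some patients, the same average rate leaves more complete profiles than the table shows.

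**With LOCF.** Every patient with an entry value has a filled profile, so the exclusion is zero. A patient seen only at entry would have that value repeated over all 36 months. Carried values would be more common in the control arm, since 25% against below 20% are expected to leave. The direction of bias cannot be fixed from the documents. Freezing a good value hides later decline, while freezing a value from a bad spell hides recovery.

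**The case against.** The strongest reply is that the abstract names LOCF as part of the primary method. If it covers all outcomes, no patient with an entry value is excluded and intent to treat is formally kept. That stands, and it is why the exclusion can only be stated conditionally. It does not rescue the analysis: the section that specifies the tests omits LOCF, and carrying values forward under unequal attrition is a weak basis for a three-year comparison.

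A reader might infer that the ANOVA would lose about half the patients. The documents do not support that. They give attrition but no missed-visit rate, and half is reached only by assuming about 3.6% missed per quarterly visit or about 7% per six-monthly visit. A reader might also infer that the all-evaluations promise cannot be met at all. That fails too, since under LOCF every observed evaluation can enter.

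Three further points limit the scope, and all stand.

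- The primary comparisons use chi-square and a t-test or Wilcoxon test, so they are untouched. Continuous outcomes are also to be analysed by regression with covariates.
- A final assessment is sought from patients who withdraw, and medical files are to supply many outcome measures for those who leave treatment but consent to use of their data. This may reduce the gaps, but it does not assure a value at every scheduled visit.
- Sphericity is no finding. Corrections for it are standard and can be left to an analysis plan that is not shown.

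**Conclusion.** The point holds for the longitudinal secondary outcomes only. Without imputation, the named method would exclude about 20% to 22.5% of patients, up to about 50 of 220, unequally by arm and against the section's own commitment. The upper figure is the protocol's expected attrition with the experimental arm at its ceiling; the lower one assumes 15% there. Isolated missed visits would enlarge the loss: at an assumed 2% to 5% per visit, 61% to 42% of patients stay complete on quarterly scales and 69% to 57% on six-monthly scales.

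With LOCF the exclusion disappears, but the contrast rests partly on stale values, more often in the control arm. Whether this biases the result, and in which direction, depends on why patients leave and how they fare afterwards, which the documents cannot show. The selection and pattern-mixture models do not cover the gap, because they are conditional and confined to the primary analyses. The plan should be changed, but the trial's main conclusion does not depend on it.

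**What to change.** 1. Reconcile the abstract with the Statistical analyses section: say whether LOCF is used, and for which outcomes.
2. For these secondary outcomes, replace repeated-measures ANOVA, with or without LOCF, by a likelihood-based mixed model for repeated measures on all observed assessments. Include arm, visit, arm-by-visit, entry value, and the stratification factors sex and substance abuse.
3. Prespecify the within-patient covariance and a fallback. An unstructured matrix has 12 × 13/2 = 78 parameters for the quarterly scales and 6 × 7/2 = 21 for the six-monthly ones, so a more parsimonious form may be needed for the former.
4. Report the arm contrast over the three-year extension, the period in which the primary hypothesis is framed, as well as by visit.
5. Extend the pattern-mixture sensitivity analysis to these outcomes. The mixed model assumes data missing at random, and the plan itself allows that missingness may be informative.

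The cost is a change of wording and some added analysis in standard software. No new data are needed.

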### Ethical considerations

All patients randomized to either continued SEI or to regular care following two years of SEI are offered treatment according to best practice. Participants are informed about the trial and about the voluntary nature of their participation with both written and verbal communications. Participants are only randomized following the provision of informed consent.

## Trial status

Currently all participants (n = 220) have been recruited and are randomized with n = 109 in the experimental group and n = 111 in the control condition (extended SEI vs. regular care). Participants are being followed with the last patient assessments scheduled for 2015.

## Discussion

This study is based on previous data that suggests that the benefits of SEI services in FEP at two years are lost at five-year follow up if patients return to regular care [31]. Given the severity of psychosis and the individual and societal costs associated with this disorder, there is a need for research that can better guide best practices. That FEP patients are young and potentially still malleable to treatment, suggests the importance of positively influencing long-term trajectories of outcome. To our knowledge, this is the first RCT trial of its kind in North America, and one of only two such trials anywhere (OPUS-II) [61], being carried out currently to assess the impact of extended SEI for a total of five years in FEP. Several strengths of this study include the number of participants recruited as well as the computerized randomization procedure that ensures chance allocation to group. That we have included FEP patients with comorbid disorders, including comorbid substance use, and that patients in our control condition are likely to be filtered through a wide range of 1st, 2nd, and 3rd line services available, gives critical construct validity to our study. Given that the majority of service is provided out of a single site (PEPP-Montreal) with two satellite clinics that are closely aligned and that follow the same treatment system, homogeneity of service infrastructure and fidelity to the same SEI model of care is ensured. As well, we are measuring a host of critical variables that may give meaning to the context of remission. Variables including social and occupational functioning and negative symptoms at baseline have been shown to impact long-term trajectories in FEP [12,13]. Measures of quality of life bring into focus the personal perspectives of this disorder while concurrent measures of all associated economic costs will highlight societal burden. This trial is registered http://www.isrctn.com/ (ISRCTN11889976), which helps to ensure complete reporting.

A limitation of any service based trial is that we are unable to blind participants or service providers to treatment allocation. While participants may not receive their preferred allocation in either condition, this possibility is discussed beforehand. That assessors are independent of treatment providers and conduct their evaluations blind to the treatment allocation outside of the patients’ treatment location will reduce chances of unblinding the treatment assignment and ensure the integrity of symptom and functional assessments.

### Potential impact of the results

Despite the growth of SEI services across the world, the optimum length of SEI services in FEPP has not been ascertained and remains an important issue for treatment providers, service users, and policy makers. Results of this RCT are likely to have major impact on treatment of FEP and the recommendation of an optimal duration of SEI services. Should an extension of SEI serve to improve outcomes for patients with a FEP, this will be a major benefit to individuals, families and to society.

## Abbreviations

RCT: Randomized controlled trial
SEI: Specialized early intervention
FEP: First episode psychosis
PEPP: Prevention and early intervention program for psychosis
CLSCs: Community services centres
RAMQ: Regie de’lAssurance-maladie du Quebec
MUHC: McGill University Health Centre
